### **Primary efficacy analysis**

The primary analysis will be linear mixed models through which we will test for differences between treatment groups on each outcome over time, with adjustment for random variation between treatment centres, with and without adjustment for other potentially important predicts (e.g. compliance, age, gender, severity of VaD). Non-linear changes over time will be tested by a) fitting time as categorical variable and b) testing for quadratic and cubic effects. Results will be reported as regression coefficients (or odds ratios if categorical) and associated 95% confidence intervals.

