#### 3.2 Sample

##### Sample Size

Following the release of the Phase II SLT trial results, sample size for this study was recalculated as the two studies used very similar participant cohorts and study design. In particular, the Phase II study provided useful data for VADAS-cog, one of the primary outcomes for the current study. Sample size was calculated using the Phase II trial outcome data for the two primary measures (VADAS-Cog and ADCS-ADLs). Based on their VADAS-Cog data, we expect the minimum between-group endpoint to be 3 or more units (with a standard deviation of 6.56) for a clinically meaningful change in cognition. Using a one-sided independent samples t-test for the purpose of calculating sample size, a total of 166 participants are required to detect this difference with 90% power at the 0.05 significance level. For the ADCS-ADLs, we anticipate the minimum between-group endpoint to be 3 or more units (with a standard deviation of 5.31) for a clinically meaningful change in daily functioning. Using a one-sided independent samples t-test for the purpose of calculating sample size with this measure, a total of 110 participants are required to detect this difference with 90% power at the 0.05 significance level. Allowing for a total non-compliance/withdrawal rate of 30%, 238 participants will be recruited into the trial across all centres to ensure 166 participants in the final analyses.

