## **Drug Accountability**

On an ongoing basis all study drugs will be reconciled against delivery, use and returned medication documents. Study drugs which are not used may be destroyed in a suitable facility locally after drug accountability has been completed and with confirmation from the coordinating chief investigator. To be compliant with the treatment protocol study, drug dosing must have a compliance rate of at least 70% over the 52-week study period. Treatment compliance will be calculated by dividing the actual number of capsules taken with expected number of capsules to be taken for the treatment period and multiplying by 100. Self-reported measures of compliance will involve asking participants and their study partner/carer to complete a diary between visits. The researchers will also ask about their adherence to the prescribed treatment regime at the week 4, 13, 26, 39 and 52 visits.

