### **Missing data and protocol violations**

In the case of death, all measurements prior to death will be included in the analysis but all after death will be set to missing. To address withdrawals, loss to follow-up or non-compliance with the study analyses will be conducted on both an intention to treat (ITT) and per protocol (PP) basis. Withdrawing and non-compliant participants shall be encouraged to continue with data collection even if stopping treatment. Where data items are missing the last value carried forward method to replace missing data in the ITT analysis will be used. Participants who have significant deviations from the protocol will be removed from the PP analysis after the completion of the ITT analysis. Such significant deviations from the protocol will be determined and documented by the study clinician during the course of the study. Any deviation from randomisation, missing data and withdrawals will be fully reported for this purpose.

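### Compliance, which is measured after randomisation, is listed as a covariate for the adjusted version of the primary mixed model

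*Protocol*

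**What the plan says.** In section 5.2 of the protocol, the part on the primary efficacy analysis sets out the model as follows: "The primary analysis will be linear mixed models through which we will test for differences between treatment groups on each outcome over time". Random variation between centres is allowed for, and the model is to be fitted "with and without adjustment for other potentially important predicts (e.g. compliance, age, gender, severity of VaD"). Compliance is the first example in that list and stands beside characteristics known at entry.

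Protocol section 3.3, Drug Accountability, defines compliance by "dividing the actual number of capsules taken with expected number of capsules to be taken for the treatment period", expressed as a percentage. A participant counts as compliant with a "compliance rate of at least 70% over the 52-week study period". Staff also ask about "adherence to the prescribed treatment regime at the week 4, 13, 26, 39 and 52 visits". All of these visits come after baseline.

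Section 5.2, Missing data and protocol violations, deals with non-compliance by another route: "non-compliance with the study analyses will be conducted on both an intention to treat (ITT) and per protocol (PP) basis".

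**The concern.** Randomisation balances the arms on what is fixed before allocation. It does not balance them on behaviour during treatment. Compliance can respond to treatment, through tolerability or perceived benefit. It can also share causes with outcome: participants have MMSE scores of 10 to 24, and the inclusion criteria require a study partner able to help them comply. If both links exist, holding compliance fixed compares participants who differ in ways other than allocation, and it may also remove part of the effect of being assigned to SLT. The adjusted coefficient is then no longer the intention-to-treat effect.

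There is also a question of timing. The primary endpoint includes week 26. If the 52-week compliance figure is the covariate, week 26 scores are adjusted for behaviour that partly comes later.

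At stake is the meaning of one of the two fits that the protocol places under its primary analysis heading.

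**Working it through.** **1. The protocol's own figures.** The sample size section takes "the minimum between-group endpoint to be 3 or more units (with a standard deviation of 6.56") for VaDAS-cog and an SD of 5.31 for ADCS-ADL, with a one-sided 5% t-test and 90% power. The two-sample t calculation with 1:1 allocation gives 166 and 110, as stated. Inflation for 30% loss gives 166 / 0.70 = 237.1, rounded up to 238, as stated. None of these figures involves compliance.

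**2. Is compliance a baseline variable?** No. Its numerator and denominator are capsule counts over the treatment period, and the first adherence question comes at week 4. Age and gender are fixed at entry, and severity is a baseline variable if measured before randomisation.

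**3. Shift in a model with one outcome value or one change score per participant.**

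- The identity is: adjusted effect = unadjusted effect − b × (difference in mean compliance between arms).
- Here b = r × SD(outcome) / SD(compliance), the within-arm slope of outcome on compliance.
- With a = difference in mean compliance / SD(compliance), the size of the shift is r × a × SD(outcome).

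The SD of 6.56 is the protocol's. The protocol gives neither r nor a, so both are assumptions.

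| r (assumed) | a (assumed) | Shift in VaDAS-cog points | Share of the 3-point difference |
|---|---|---|---|
| any | 0 | 0 | 0% |
| 0.10 | 0.1 | 0.10 × 0.1 × 6.56 = 0.07 | 2% |
| 0.25 | 0.3 | 0.25 × 0.3 × 6.56 = 0.49 | 16% |
| 0.25 | 0.5 | 0.25 × 0.5 × 6.56 = 0.82 | 27% |
| 0.40 | 0.5 | 0.40 × 0.5 × 6.56 = 1.31 | 44% |

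The direction depends on the signs of r and of the difference between arms.

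**4. Simulation of the same model.** Assumptions: 166 participants, no true treatment effect, outcome SD 6.56, compliance SD 10 percentage points, one unmeasured health factor driving both compliance and outcome, and a two-sided 5% test.

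- Equal mean compliance: the adjusted estimate is centred near 0 and the false-positive rate is about 5%.
- Compliance 5 points lower on active (a = 0.5) and a within-arm correlation of −0.25: the adjusted estimate averages −0.8 and the false-positive rate is 12%.
- The unadjusted fit stays near 0, with a false-positive rate of 4.4% to 5.7% across all settings.

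**5. Does this carry over to the planned mixed model?** That depends on its form. Take a random-intercept model with group, time as categories (weeks 0, 26 and 52) and their product, fitted to 166 participants with complete data, no true effect and compliance 0.3 SD lower on active. Adding compliance as a main effect leaves the week 52 group-by-time contrast unchanged to rounding error. Adding compliance by time as well moves it by about 0.5, in line with the 0.49 in the table. The protocol does not say in which form compliance would enter.

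**The case against.** The strongest reply is that the plan fits the model both with and without covariates, and that compliance is only an example in an open list. A valid randomised comparison therefore exists whatever the adjusted fit shows. That is correct, and it limits the point to the adjusted fit.

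Second, a reader might infer that the adjusted result is bound to be biased. The documents do not support this. The formula gives exactly zero when mean compliance is equal between arms, and the protocol contains no compliance data by arm.

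Third, a reader might take 0.49 points, or 16% of the target, as the cost of the written plan. It is not. It rests on assumed r and a and on a change-score or single-timepoint model. The section describes differences over time, and if that means a group-by-time contrast with a compliance main effect and complete data, nothing moves. What survives is that the endpoint is defined as change from baseline, so a change-score model, or one with compliance by time or time-varying compliance, is an equally open reading.

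Fourth, a reader might add that the protocol fails to say which fit is confirmatory. That choice is commonly left to a statistical analysis plan, which is not at hand, so it is not counted here.

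Finally, the 70% threshold is not a second fault. It defines who is compliant and does not make compliance a covariate.

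**Conclusion.** The point holds in a limited form. The protocol names a post-randomisation variable as a covariate for the adjusted version of its primary model. This is a stated choice, not a detail deferred to another document. The unadjusted fit is sound. The compliance-adjusted fit is open to bias if two conditions hold together: treatment changes mean compliance, and compliance is related to outcome within arms. The protocol cannot show whether they will hold.

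The illustrative size is 0.07 to 1.3 VaDAS-cog points for assumed r of 0.1 to 0.4 and a of 0.1 to 0.5 in a change-score or single-timepoint model. It is nil with equal mean compliance, and nil for a compliance main effect beside a group-by-time contrast in complete data. The confidence lies in the classification of compliance, not in any one of these figures.

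**What to change.** In section 5.2, Primary efficacy analysis, delete compliance from the covariate examples. State that adjustment in the primary intention-to-treat model is restricted to variables measured before randomisation, such as age, gender and baseline severity.

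Keep compliance for the per-protocol analysis already planned under Missing data and protocol violations, or for a supplementary analysis clearly labelled as such. The per-protocol analysis also selects on behaviour after randomisation, so it should be read as supportive.

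The cost is a change of wording, best made before the data are unblinded. Data collection, the visit schedule and the stated sample sizes of 166, 110 and 238 are unaffected.

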### **Subgroup analyses**

Secondary analyses will be a repeat of the above stratified by disease type and, if necessary, with stratification by research centre.

Data will be analysed using SAS and/or SPSS software.

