### Participant Characteristics

To achieve the aim of this study, it is desirable that the participant group is relatively homogenous with regard to health profile and disease risk factor presentation to ensure internal validity of the results. However, a broad representation of Australian adults according to demographic and social factors will be sought to improve generalisability of the study findings

for the community. The total number of participants with AD+CVD should not exceed a third of the sample size. Participants of each gender, a wide range of ages, ethnic and social backgrounds will be represented in this study.

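### Disease type is analysed only by repeating the primary model within VaD and within AD+CVD, which does not test whether the SLT effect differs by diagnosis; no treatment-by-disease-type interaction is stated.

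*Protocol*

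**What the plan says.** The Subgroup analyses paragraph of section 5.2 gives the method for diagnosis in one sentence: "Secondary analyses will be a repeat of the above stratified by disease type". It adds stratification by research centre where needed. The analysis to be repeated is the one under Primary efficacy analysis, namely "linear mixed models through which we will test for differences between treatment groups on each outcome over time", and for that analysis "Results will be reported as regression coefficients (or odds ratios if categorical) and associated 95% confidence intervals".

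Section 3.2, Participant Characteristics, limits one of the two diagnoses: "The total number of participants with AD+CVD should not exceed a third of the sample size". Section 3.3 describes randomisation in permuted blocks of six, three active and three placebo, with no stratification by diagnosis.

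Centre is handled differently. Under Checking for homogeneity of study centres, section 5.2 fits models to each outcome with centre and a centre-by-treatment term as fixed effects, with sensitivity analyses to follow if needed. No matching term is stated for disease type anywhere in the protocol.

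**The concern.** Two separate fits answer two questions: is there an effect in VaD, and is there an effect in AD+CVD? Neither asks whether the effect differs between them. Because AD+CVD can be at most a third of the sample, its estimate is less precise by design, and it will often miss significance when VaD does not, even if the true effect is identical.

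The trial's objectives cover both diagnoses, so whether SLT works in each is an obvious question for any reader of the results. With only within-stratum results, that question invites a comparison of significance across strata, which is an unreliable guide. The protocol uses the suitable tool for centre but not for diagnosis, the only clinical subgroup it names.

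**Working it through.** **Inputs.** From section 3.2, Sample Size:
- VaDAS-cog: "we expect the minimum between-group endpoint to be 3 or more units (with a standard deviation of 6.56".
- ADCS-ADL: "we anticipate the minimum between-group endpoint to be 3 or more units (with a standard deviation of 5.31".
- Test: "Using a one-sided independent samples t-test for the purpose of calculating sample size".
- Result: "a total of 166 participants are required to detect this difference with 90% power at the 0.05 significance level". The ADCS-ADL total is 110, and 238 are recruited to allow for 30% loss.

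The one-third cap comes from Participant Characteristics. The two-sided 5% level used for the main figures is inferred from the 95% confidence intervals in section 5.2; one-sided figures are given alongside.

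**Assumptions.** Same true effect and SD in both strata; 1:1 arms within strata; a t-test at one time point as a proxy for the mixed model.

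**1. The plan's own figures.** A one-sided two-sample t-test at 0.05 with 90% power gives 166 in total for VaDAS-cog (d = 3/6.56 = 0.457) and 110 for ADCS-ADL (d = 3/5.31 = 0.565). Then 166/0.70 = 237.1, which rounds up to 238 for equal arms. All three figures are reproduced. A two-sided test would give 204 and 134.

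**2. Strata at the cap.** 166/3 ≈ 55 AD+CVD, leaving 111 VaD, or about 27.5 and 55.5 per arm.

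**3. Power within each stratum** (VaDAS-cog, effect 3, two-sided 5%, noncentral t): VaD 0.666, AD+CVD 0.384.

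**4. Chance that exactly one stratum is significant.** The strata are independent, so P = p₁(1 − p₂) + p₂(1 − p₁):
- VaD only: 0.666 × 0.616 = 0.410
- AD+CVD only: 0.384 × 0.334 = 0.128
- Exactly one: 0.410 + 0.128 = 0.538, or 54% (a simulation of 200,000 runs gave 53.8%)
- Both: 0.666 × 0.384 = 0.256; neither: 0.334 × 0.616 = 0.206

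**5. Other cases.** Same formula, true effect 3 in both strata, chance that exactly one is significant:

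| Outcome | N analysed | AD+CVD share | Two-sided 5% | One-sided 5% |
|---|---|---|---|---|
| VaDAS-cog | 166 | 1/3 | 54% | 49% |
| VaDAS-cog | 166 | 20% | 62% | 59% |
| VaDAS-cog | 238 | 1/3 | 49% | 39% |
| VaDAS-cog | 238 | 20% | 62% | 53% |
| ADCS-ADL | 166 | 1/3 | 47% | 37% |
| ADCS-ADL | 166 | 20% | 62% | 52% |
| ADCS-ADL | 238 | 1/3 | 32% | 22% |

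The rows with 238 are included because section 5.2 carries the last value forward in the ITT analysis, so the number analysed may be nearer 238 than 166.

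Varying the common true effect (VaDAS-cog, 111 and 55, two-sided) gives 41% at 2 points, 54% at 3, 42% at 4 and 22% at 5.

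**6. The interaction instead.** SE = 6.56 × √(2/27.5 + 2/55.5) = 2.16 points, so the 95% CI half-width is 1.96 × 2.16 ≈ 4.2. With equal true effects the test rejects about 5% of the time (simulated 4.9%). Its power against a true 3-point difference between diagnoses is about 28%, and 80% power would need a difference of about 2.80 × 2.16 ≈ 6.1 points.

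**The case against.** The strongest reply is that the paragraph is a one-sentence outline of analyses labelled secondary. Stratified estimates are compatible with an interaction test, nothing excludes one, and a SAP that is not shown may add it. That limits the severity but does not remove the point. The protocol names a method for diagnosis, and that method does not address whether the effect differs. A SAP would have to supplement it.

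Three stronger readings are tempting, and the documents do not support them.

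- A reader might infer that a split verdict is more likely than not in general. It is for VaDAS-cog with 166 evaluable, two-sided, at the cap and a true effect near 3, and the chance rises if fewer AD+CVD participants enrol. At the cap it is below one half one-sided, for ADCS-ADL, and with 238 analysed. It is also below one half for true effects of about 2 or less, or 4 or more.
- A reader might infer that the protocol plans to compare stratum p-values. It does not say so; it reports coefficients with 95% confidence intervals. The split in question is only significance in one stratum and not the other. Estimates of opposite sign would occur in only about 5% of trials at a one-third share and 10% at a 20% share.
- A reader might extend the point to centre. The centre-by-treatment term in section 5.2 already covers that, and stratifying by centre is conditional.

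**Conclusion.** The point holds in a limited form. Repeating the model by stratum does not test whether the SLT effect differs by diagnosis, and no interaction for diagnosis is stated. Under the planning effect, and if significance were compared across strata, a split result would arise by chance about half the time for VaDAS-cog and in roughly a third to a half of trials for ADCS-ADL at the cap (two-sided). The one-sided range at the cap is 22% to 49%. Even the lowest of these is well above the 5% false-signal rate of an interaction test.

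The exact percentages depend on the assumptions listed with the calculation, and a longitudinal mixed model will shift them somewhat. The direction does not depend on them. Since the analysis is secondary and the primary comparison is unaffected, this is a change that should be made, not one on which the trial's validity turns.

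**What to change.** In section 5.2, Subgroup analyses, replace the stratified repeat for disease type as follows:
- Fit the full-sample primary model with treatment-by-disease-type (by visit) terms.
- Report the interaction estimate with its 95% CI as the basis for any claim that the effect differs by diagnosis.
- Present stratum-specific effects from the same model, with CIs, as descriptive.

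State the limit alongside. For VaDAS-cog with 166 evaluable at the cap, the interaction has an SE of about 2.2 points and about 28% power for a 3-point difference, so a non-significant interaction must not be read as showing equal effects. The text on centre needs no change.

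The cost is a sentence or two in section 5.2, with no new data, participants or procedures.

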## **6. TIMEFRAME**

| Month                                                   | 1-6 | 7-12 | 13-18 | 19-24 | 25-30 | 31-36 | 37-42 | 43-48 |
|---------------------------------------------------------|-----|------|-------|-------|-------|-------|-------|-------|
| Actives and placebo preparation                         |     |      |       |       |       |       |       |       |
| Engagement of staff, final preparation, ethics approval |     |      |       |       |       |       |       |       |
| Recruitment                                             |     |      |       |       |       |       |       |       |

|                            |  |  |  |  |  |  |  |  |
|----------------------------|--|--|--|--|--|--|--|--|
| Intervention and follow-up |  |  |  |  |  |  |  |  |
| Data entry and analysis    |  |  |  |  |  |  |  |  |
| Publications, Final Report |  |  |  |  |  |  |  |  |

Table 2. Research Timeline

## **APPENDIX 1**

### **Adverse Event Definitions**

The following definitions are from International Harmonised Tripartite Guidelines and used as the TGA clinical trial guidelines.

#### Adverse Event

An Adverse Event is any untoward medical occurrence in a patient or clinical investigation subject administered a pharmaceutical product and which does not necessarily have a causal relationship with the treatment. An Adverse Event can therefore be any unfavourable and unintended sign, symptom or disease temporally associated with the use of a medicinal (investigational) product, whether or not related to the medicinal product.

#### Severity of Adverse Event

Mild Adverse Event: The event causes minimal discomfort and does not significantly interfere with the patient's normal activities.

Moderate Adverse Event: The event is sufficiently uncomfortable to cause some impairment to the participant's normal activities.

Severe Adverse Event: The event is incapacitating and prevents the participant from participating in normal activities.

#### Serious Adverse Event

A Serious Adverse Event is any untoward medical occurrence that at any dose:

- 1) Results in death
- 2) Is life threatening (at immediate risk of death at the time of the event and does not mean an event which hypothetically might have caused death if it was more severe of caused permanent or significant disability / incapacity)
- 3) Requires inpatient hospitalisation or prolongation of existing hospitalisation
- 4) Results in persistent or significant disability/ incapacity
- 5) Leads to a congenital anomaly or birth defect

- 6) Leads to events that require medical or surgical intervention to prevent permanent impairment of function or damage to body structure

Severe refers to the severity of the event at the time as opposed to the seriousness of the participant's event outcome e.g. a headache might be severe and disabling but not serious. A mild heart attack though not disabling at the time has more serious health consequences.

